## Methods

### Study design

This protocol paper has been written in line with the standards of Standard Protocol Items: Recommendations for Interventional Trails (SPIRIT) [16]. We will perform a multicenter prospective cohort study with patients who have decided to be given a total KA (TKA) or a unicompartmental KA (UKA). To establish generalizability, the BAAS pathway will be performed in two high-volume KA hospitals in the Netherlands serving a representative population of working patients receiving KA. For the effectiveness of BAAS regarding RTW, the results of the study will be matched in pairs and compared to individual patient data on RTW by matched pairs from prospectively performed cohort studies in the Netherlands on care as usual, namely the Expect to Work cohort and the ACTIVE trial [17, 18]. For the economic evaluation, a comparison will be made with individual patient-level data using the care-as-usual group of the ACTIVE trial in the Netherlands [17]. The study has been approved by the Medical Ethical Committee of the Amsterdam UMC, location AMC (reference ID: W21_454 # 21.504) and the Medical Ethical Committees of the local hospitals Nij Smellinghe (NS, reference ID: 19,888) and Elizabeth Tweesteden Ziekenhuis (ETZ, reference ID: L1429.2021).

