#### Recruitment

Inclusion criteria for patients are: (ii) being scheduled for primary or revision UKA or TKA by an orthopedic surgeon between January 2022 and July 2023; (ii) having paid work for at least eight hours a week before surgery; (iii) being between 18 and 65 years of age and (iv) having the intention to fully RTW after surgery. Criteria to exclude patients are: (i) receiving more than one medical event within one year that affects work ability after KA; (ii) having a KA for any other reason than knee osteoarthritis; and (iii) having major disabling mental disorders. Patients who do not speak or read Dutch are given the opportunity to fill in the questionnaires with the aid of a translator and to have an interpreter present during the consultations. Patients who are eligible to participate are informed about the study by telephone by the medical case manager (MCM; physical therapist working in the hospital). During an intake consultation with an MCM, the patient information letter, informed consent, and an infographic of the BAAS clinical pathway (Additional file 1: Appendix I) are handed out to the patient. Patients’ questions regarding participation are answered. Patients are given one week to decide whether or not they wish to participate. Patients who opted for the possibility to participate receive a telephone call after one week so that they can ask any additional questions about the study and they will be asked if they want to participate. Participants willing to participate sign the informed consent.

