### Statistical methods

#### Effectiveness

The effect of the BAAS care pathway on time to RTW will be statistically tested using survival analysis and gamma regression analysis including bootstrapping using R (version 4.1.0). Missing data will be handled by multivariate imputation using the aforementioned prognostic factors if possible [46]. For the repeated measurements on the time to RTW and/or full RTW, a mixed model will be used to test and estimate the size of the BAAS effect controlling for the following potential prognostic factors of delayed RTW, namely UKA vs TKA, primary vs revision KA, gender, BMI, physical nature of the job, preoperative sick leave, and patient-reported work-relatedness of knee symptoms. Hazard ratios including 95% confidence intervals will be calculated for the intervention group and tested against both control groups. In the absence of an empirically derived MCID, a difference of two weeks will be considered clinically relevant for first day of RTW and one week for full RTW. For interpreting the magnitude of the standard mean difference (SMD), three groups are defined: (i) small (SMD = 0 – 0.2); (ii) medium (SMD = 0.2 – 0.5) and (iii) large (SMD = 0.5–1.0) [47]. Sensitivity analyses on RTW will be performed for the two hospitals. Analyses will be conducted using both univariate and multivariate analyses to assess the effect size of the BAAS care pathway with and without controlling for variables. Lastly, because this control group is not from the same cohort as the intervention group, we will use propensity analysis (matched pairs) to correct for other confounding factors [48]. Potential prognostic factors for delayed RTW like UKA vs TKA gender, BMI, physical nature of the job, preoperative sick leave and patient-reported work-relatedness of knee symptoms will be used for patient matching. Secondary outcomes will be plotted in time and will be tested on differences between the usual care cohorts and the intervention cohort.

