In transition processes, in which care as usual is replaced by a new care pathway, the essential role of the patients and health care professionals is often overlooked. Therefore, in our study the professionals involved in the care transitions in the two hospitals will collect and scrutinize the data together and, based on the results, determine what kind of action should be performed to enhance RTW in close contact with the patient. One of the consequences of this iterative cycle will be that all professionals as well as the patients involved become partners in achieving an optimal RTW. This way, the embedded scientist who, in daily practice, collects, creates, and reviews knowledge, and investigates the effectiveness of this newly implemented care pathway is an essential actor in creating and implementing future RTW pathways for other groups of working age patients.

Lastly, by using the data from two Dutch cohorts on RTW with similar inclusion criteria, our study is designed to be more cost-effective than a randomized controlled trial.

The limitations of this study protocol are that the lead author has an active role as an MCM in this study. This is why we included patients from a second hospital (ETZ). Also, we will not perform an RCT. We will use the data from two other prospective cohort studies with similar inclusion criteria to compare our findings to usual care. The care for knee arthroplasty is, fortunately, largely standardized in the Netherlands [44, 53]. Also, we will use propensity analysis to reduce the bias due to possible differences between our cohorts and the two comparison cohorts [17, 18].

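### BAAS requires an intention to return fully to work, but the plan neither shows that both comparator cohorts did nor controls for it in matching

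*Protocol article*

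**What the plan says.** Under Recruitment, the fourth inclusion criterion for BAAS patients is "having the intention to fully RTW after surgery". The section also sets conditions on paid working hours, age, indication and mental disorder.

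Under Study design, usual-care data come from outside the study, "namely the Expect to Work cohort and the ACTIVE trial". Primary outcomes assigns the first cohort to first day of return and the ACTIVE comparison group to full return. The economic evaluation also uses the ACTIVE usual-care group.

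On the eligibility of these cohorts, the Discussion says: "We will use the data from two other prospective cohort studies with similar inclusion criteria to compare our findings to usual care". No criterion of either cohort is listed.

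Under Effectiveness, the remedy for differences between cohorts is stated as "we will use propensity analysis (matched pairs) to correct for other confounding factors". The factors are given as "Potential prognostic factors for delayed RTW like UKA vs TKA gender, BMI, physical nature of the job", followed by "preoperative sick leave and patient-reported work-relatedness of knee symptoms will be used for patient matching". The Economic evaluation section repeats the same factors. The adjusted model controls for "UKA vs TKA, primary vs revision KA, gender, BMI, physical nature of the job, preoperative sick leave, and patient-reported work-relatedness of knee symptoms".

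**The concern.** Full return to work is a primary outcome, and the intention to achieve it is a condition of entry to BAAS. A patient who does not intend to return fully can be expected to do so later on average, or not at all, whatever the care. There is no concurrent or randomised control, so aligned eligibility and matching are what make the comparison fair. The article fixes the entry criterion, the comparators and the named matching factors, but nothing in it connects the first to the other two.

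If either comparator contains patients without the intention, part of the difference between pathway and usual care would come from who was enrolled. The direction favours BAAS: longer control times to full return, and more sick-leave days in the control costs. Because the return-to-work outcomes use different comparators, alignment has to be shown for each cohort separately.

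**Working it through.** The plan gives no figure on this point to reproduce. The check sets the entry conditions against the stated controls for confounding and then asks what matching can do.

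**Step 1. Entry conditions against the named factors.**

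| BAAS entry condition (Recruitment) | Comparator criterion listed in the article? | Named matching factor? | Model covariate? |
|---|---|---|---|
| Intention to return fully | No | No | No |
| At least 8 hours' paid work a week | No | No | No |
| Age 18 to 65 | No | No | No |
| Osteoarthritis as the indication | No | No | No |
| No major disabling mental disorder | No | No | No |
| UKA or TKA, primary or revision | No | UKA/TKA only | Both |

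The Demographics section contains no item on intention or expectation either. None is needed on the BAAS side, where the criterion makes intention constant. What matters is whether it was required or recorded among controls. Study design describes the external individual data as data on return to work and does not say whether intention was recorded.

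**Step 2. What matching can remove.** Let X be the named matching factors. By design, every BAAS patient has the intention at every value of X. Let f be the share of matched controls without it. Matching balances X. It lowers f only as far as X predicts intention, and it does not force f to zero.

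**Step 3. Bias in mean time to return.** Suppose the pathway has no effect. Let m be the mean time for patients with the intention, and let controls without it return w weeks later on average.

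- BAAS mean: m
- Control mean: (1 − f) × m + f × (m + w) = m + f × w
- Apparent benefit of BAAS: f × w

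**Step 4. Illustration.** Neither f nor w is in the document. Both are assumptions, shown over a range.

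| f | w = 10 weeks | w = 20 weeks |
|---|---|---|
| 0% | 0 | 0 |
| 5% | 0.05 × 10 = 0.5 weeks | 0.05 × 20 = 1.0 week |
| 10% | 0.10 × 10 = 1.0 week | 0.10 × 20 = 2.0 weeks |
| 20% | 0.20 × 10 = 2.0 weeks | 0.20 × 20 = 4.0 weeks |

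The Effectiveness section treats one week as relevant for full return and two weeks for first return. The one-week threshold is therefore reached at f = 1/10 = 10% when w is 10 weeks, and at f = 1/20 = 5% when w is 20 weeks. The table concerns means. It does not carry over directly to the planned hazard ratios, where patients who have not returned would normally be censored.

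**The case against.** **Similar may mean the same.** The strongest objection is that the comparators' eligibility lists are not shown, and similar criteria are compatible with both cohorts having required the same intention. In that case f is zero at entry and nothing needs matching. This stands, and it is why the point is conditional. A reader might infer that the criterion applies to one side only, or that unwilling returners are in the control data. The document does not support either statement. Nor does it show that the conditions on hours, age, indication or mental disorder differ.

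**A condensed article.** Construction of the control set may be detailed in a fuller document, and the matching list is introduced by the word like, so it is not closed. This stands in part. An open list allows for intention but does not commit the team to it, and the article itself pairs an entry criterion tied to the outcome with named factors that leave it out.

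**Already disclosed.** The Discussion concedes possible differences between cohorts. It then relies on propensity analysis to reduce them, and on the named factors that analysis cannot remove a difference in intention.

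**A firmer magnitude.** A reader might take the Discussion's figure that 49% needed more than six months for full return, place the usual-care median near 183 days, and argue that controls staying out to day 365 (365 − 183 = 182 days longer) need make up only 7/182 = 3.8% of the group to create one week. The document does not support this. The 49% comes from a cohort that is not a comparator here, a median stands in for a mean, and the share of such controls is unknown.

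**Reduced hours.** Full return is defined by contract hours, so a patient who planned fewer hours and changed contract could still meet it. Not intending to return at all is the cleaner example.

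**Conclusion.** The point holds in conditional form. The article makes intention to return fully a BAAS entry condition, describes the comparators' criteria only as similar, and names no matching factor or covariate for intention. If either comparator did not require the intention, the stated remedy cannot correct the difference, and the bias would favour BAAS on time to full return and on absenteeism costs. If both required it, this source of bias is absent at entry.

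The size cannot be derived from the document. The illustrative range of 0 to 4 weeks rests wholly on assumed values of f and w. It shows that modest values can reach the plan's relevance thresholds and does not estimate the bias. The direction rests on the assumption that patients without the intention return later on average.

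The change is worth making because restriction to eligible controls alters nothing if the criteria are identical, and removes a bias in favour of the intervention if they are not and the data allow it.

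**What to change.** 1. List each comparator cohort's eligibility criteria beside those of BAAS.
2. Before propensity matching, apply the BAAS baseline inclusion and exclusion criteria to the individual data of each comparator, and match only within that eligible set. Do this for both return-to-work comparisons and for the economic evaluation. Use only what could be judged at baseline, so that controls are not selected on later events.
3. Where a comparator did not require intention but recorded it, or recorded a preoperative expectation of return, restrict or match on that item.
4. Where neither exists, say so and report a bounding analysis for unmeasured confounding, for example the values of f and w at which the estimated effect would fall below the relevance threshold. It should not remove non-returning controls: that selects on the outcome in one group only and would bias against BAAS.

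The cost is a short table, a filter and a few sentences, with possibly fewer controls available for matching. Steps 2 and 3 depend on what the comparators recorded, which the article does not state.

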## Data Availability

The datasets used and/or analyzed during the current study are available from the corresponding author on reasonable request.

## Abbreviations

BAAS: Back At work After Surgery
BMI: Body Mass Index
CHEERS 2022: Consolidated Health Economic Evaluation Reporting Standards 2022
CI: Coincidence interval
CSI: Central Sensitization Inventory
DEMMI: De Morton Mobility Index
ETZ: Elizabeth Tweesteden hospital Tilburg
FTST: Five Time Sit to Stand Test
GAS: Goal Attainment Scaling
ICC: Inter rater correlation
IPCQ: IMTA Productivity Cost Questionnaire
KA: Knee arthroplasty
KNGF: Royal Dutch Society for Physiotherapy
KOOS: Knee Injury and Osteoarthritis Outcome Score
MCID: Minimal clinical important difference
MCM: Medical Case Manager
MDC: Minimal detectable change
NS: Nij Smellinghe hospital Drachten
OCM: Occupational Case Manager
RTW: Return to work
SPIRIT: Standard Protocol Items: Recommendations for Interventional Trails
STROBE: Strengthening the Reporting of Observational Studies in Epidemiology
TKA: Total Knee Arthroplasty
UKA: Unicompartmental Knee Arthroplasty
WAI: Work Ability Index
WAS: Work Ability Score
WORQ: Work, Osteoarthritis and Joint-Replacement Questionnaire
30-STST: 30 Second Sit to Stand Test
6 MWT: 6-Minute walk test
